#### Exclusion Criteria

Individuals who met any of the following criteria were excluded from participation:

##### Practicalities and Participation

Practical and participation-related factors, of one (or more) of the following:

Concurrent participation in other intervention trials;No access to technological infrastructure (ie, computers, smartphones, mobile applications, and internet access) because the intervention is primarily online (eg, online support groups and mobile apps);Cognitive impairment, as determined by a score lower than 23 points on the Telephone Interview for Cognitive Status (TICS-M1) [113], performed during prescreening before inclusion.

##### Clinical Diagnoses and Medical History

Clinical diagnosis by a certified doctor or general practitioner of one (or more) of the following:

Cerebrovascular event (eg,transient ischemic attack, cerebral hemorrhage, and stroke);Neurological disease (eg, mild cognitive impairment, multiple sclerosis, Parkinson disease, and epilepsy);Current malignant disease, with or without current treatment;Current psychiatric disorder (eg, depression, psychosis, and bipolar episodes);Symptomatic, moderate to severe cardiovascular disease (eg, stroke, angina pectoris, heart failure, and myocardial infarction);Revascularization surgery in the last 12 months at the moment of prescreening;Inflammatory bowel disease (characterized by diarrhea);Visual impairment, which is uncorrectable with visual aids (eg, total or partial blindness);Hearing or communicative impairment, which is uncorrectable with hearing aids;

##### Magnetic Resonance Imaging Safety–Specific Criteria

Contraindications for magnetic resonance imaging (MRI), of one (or more) of the following:

Metal objects located in the upper body (exceptions: tooth fillings and dental crowns);Metal splinters in the body, in particular within the eyes (eg, through labor work in the metal industry);Jewelry items or piercings that cannot be taken off;Undergone brain surgery in the past;Active implants within the body (eg, pacemaker, neurostimulator, internal insulin pump, internal hearing aids that cannot be removed);Medical plasters or patches which cannot or may not be taken off (eg, nicotine patch);Self-reported claustrophobia.

### Interventions: Description

In the HELI multidomain lifestyle intervention, five distinct lifestyle domains were combined, namely (1) diet, (2) physical activity, (3) stress management and mindfulness, (4) cognitive training, and (5) sleep. The intervention period was 6 months (26 weeks) in total, which was subsequently followed by the follow-up outcome measure visits (see Figure 3 for an overview).

**Figure 3. F3:**
[figure not shown]
Intervention overview. HUBV (Houd uw Brein Vitaal; “Keep your brain fit”) and iSLEEP are validated psychoeducational and cognitive behavioral therapy programs.

The high-intensity intervention group received a structured and personalized intervention program consisting of weekly group sessions, active guidance from an intervention supervisor, and lifestyle domain–related individual and group exercises. The low-intensity intervention group received access to general lifestyle-related health information in an individual context, provided through information leaflets sent by email once every 2 weeks. To promote intervention adherence and blinding, we adopted the FINGER-NL [108] and US POINTER approach [114] of framing both groups as lifestyle intervention recipients, instead of using the label “control group.” The groups differ in intervention structure, engagement, and intensity rather than treatment versus control.

During communication with participants, we refrained from using the terms “high-intensity” and “low-intensity” to promote group blinding as much as possible. Instead, the intervention arms were called “weekly group sessions” for the high-intensity intervention group, and “independently working on your lifestyle” for the low-intensity intervention group. An extensive description and overview of the multidomain lifestyle intervention groups is provided below and depicted in Figure 3.

#### High-Intensity Group

##### Design

In order to achieve the domain-specific goals and ambitions, we provided participants within the high-intensity group with three key intervention elements: (1) weekly online or on-site group sessions to provide information, exercises, and personalized advice, (2) an extensive information folder containing supporting lifestyle-related information, exercises, and relevant practical information, and (3) access to an online dashboard with a personal intervention environment. Each weekly group session took approximately 90 minutes. We expected that participants required an average of 90 minutes to put additional work in the provided lifestyle advices, exercises, and other practical aspects (eg, reading online dashboard and intervention information folder; see S3.1 in Multimedia Appendix 1), resulting in a weekly expected intervention effort of 180 minutes.

##### Group Sessions

The weekly group sessions were offered throughout the 6-month (26 weeks) intervention period. For 20 out of 26 weekly sessions, a specific lifestyle domain acted as the central theme for a given week (Figure 3). At week 1, after the baseline measurements of all participants in a wave and subsequent randomization had been concluded (T0), the intervention started off with an on-site introductory session.

The weekly group sessions provided participants with detailed lifestyle-related information, guidelines, exercises, and advice, as well as the opportunity for discussion with other group members and with the intervention supervisor. Weekly group sessions were guided by the intervention supervisor and were composed of the following recurring elements: social interaction, introductory question round, reiteration of previous lifestyle domains, dissemination, exercises, and a final question round (see Table S1 in Multimedia Appendix 1 for further details).

Over the 6-month intervention period, each of the five lifestyle domains was addressed in separate weekly group sessions (see Figure 3). We provided three distinct types of weekly group sessions:

“Information sessions” primarily focused on giving general instructions, advice, and exercises on a particular domain. During information sessions, participants were encouraged to ask questions and share experiences, problems, or advice with the group.“Boost sessions” primarily focused on recalling and reiterating domains which had been discussed in previous information or booster sessions, whilst also providing smaller amounts of new information. The main goal of boost sessions was to keep participants engaged in the multiple different lifestyle domains throughout the 6-month intervention period and remind them of instructions, advice, and exercises from previous sessions. During boost sessions, more time was reserved for repeating previously discussed material and information, group discussions, and sharing experiences, advice, or problems regarding one or more specific domains.“Exercise sessions” primarily focused on explaining and performing muscle-strengthening exercises (full-body work-out, ie, including all major muscle groups) in combination with balancing and stretching exercises in a group setting at an exercise center under the supervision of a physical exercise instructor specialized in instructing and guiding older adults. The exercise instructor provided instructions for conducting these exercises and for preventing strains or injuries.

Domains that were expected to require more instructions and guidance from the start (ie, diet and physical exercise) have two information sessions and 2 boost sessions or one information session and 2 exercise sessions, whilst domains that required less initial group and personal guidance and instruction (ie, stress management and mindfulness) had one information session and three boost sessions. The lifestyle domains of cognitive training and sleep differed from the information and boost session design, as these domains were composed of a psychoeducational program for the domain of cognition (spanning four consecutive weeks) and a sleep course module for the domain of sleep (spanning five consecutive weeks), further explained below. A more detailed explanation of the ambitions, goals, and content of the 5 lifestyle domains within the HELI lifestyle intervention is provided below and in S3.1 in Multimedia Appendix 1.

### Ambition and Goals of Lifestyle Domains

#### Diet

##### Ambition and Goals

The goal of the diet domain was to support participants to adhere to the Mediterranean-DASH Intervention for Neurodegenerative Delay (MIND) diet, a diet specifically designed to slow down aging-related cognitive decline [115], and the Dutch guidelines for a healthy diet [116] which is associated with protective effects on multiple major (chronic) diseases (eg,coronary heart disease, stroke, diabetes, heart failure, and dementia). Specifically, we use the MIND-NL diet, which is adapted to the Dutch context and serving sizes [117]. Briefly, the MIND-NL diet-specific food recommendations comprise (1) green leafy vegetables, (2) other vegetables, (3) berries and strawberries, (4) whole-grain products, (5) unsalted nuts, (6) (unfried) fish, (7) (unfried) poultry, (8) beans and legumes, and (9) olive oil. MIND-NL diet-specific food restrictions comprise (1) full-fat cheese; (2) butter and stick margarine; (3) red and processed meat; (4) take-out, fried foods, and snacks; (5) cookies, pastries, and sweets; and (6) wine and alcoholic beverages [115]. The Dutch guidelines for a healthy diet consist of adhering to a healthy diet of the five major healthy food groups (in Dutch: “de Schijf van Vijf”): (1) fruit and vegetables; (2) (unsaturated) oil and spreads; (3) dairy, nuts, fish, legumes, meat, egg, or alternatives; (4) (whole-grain) bread, grain products and potatoes; and (5) hydration (water, tea, and coffee). As an additional component to this domain, to comply with Dutch national recommendations for older adults [118,119], participants are advised to take additional vitamin D_3_ supplements throughout the intervention period (see S3.1 in Multimedia Appendix 1 for age and sex-specific advised doses). For more details on the exercises, information, and goals of the diet domain, see S3.1 in Multimedia Appendix 1.

### Physical Activity

#### Ambition and Goals

The goal of the physical activity domain was to support participants to adhere to the official 2020 WHO Physical Activity guidelines [112]. These guidelines recommend engaging in physical activity of moderate intensity (eg, swimming, running, and cycling) for at least 300 minutes per week (spread out over several days), or 150 minutes of vigorous intensity aerobic physical activity (eg, cycling at a fast pace and playing singles tennis), or an equivalent combination of moderate- and vigorous-intensity physical activity (spread out over several days). Moreover, the guidelines recommend performing muscle-strengthening activities at moderate (or greater intensity) that involve all major muscle groups at least twice a week, combined with balance exercises. Finally, the amount of sedentary behavior (eg, sitting and lying down) must be limited according to these guidelines.

### Stress Management & Mindfulness

#### Ambition and Goals

The goal of the stress management and mindfulness domain was to support participants in dealing with daily stress and becoming aware of their own thoughts and feelings, and to support participants in making brain-healthy choices regarding stress management. Participants received a selection of exercises from an evidence-based, self-guided online mindfulness training (provided through the VGZ Mindfulness Coach app [120]), as well as information regarding the potential negative effects of (chronic) stress on the body and brain, as well as practical advice on how to combat stress and improve relaxation.

### Cognitive Training

#### Ambition and Goals

The goal of the cognitive training domain was to inform participants about functional and structural changes in the aging brain, to support participants in learning about strategies that could aid in coping with cognitive changes which are a part of normal aging (eg, informing participants about memory strategies and sharing tips to improve attention capabilities), and how to ultimately apply these strategies in daily life. The cognitive strategy training was based on the Dutch “Houd uw brein vitaal!” (HUBV; “Keep your brain fit!”) psychoeducational program [121]. The HUBV program consists of 2 main parts: lifestyle and memory (complaints), and effective strategy training (see S3.1 in Multimedia Appendix 1 for a more extensive description).

### Sleep

#### Ambition and Goals

The goal of the sleep domain was to support participants in improving sleep quality (and if applicable, reduce insomnia), and to inform participants about the possible health risks associated with poor sleep in aging. Participants received a 5-week sleep counseling module using a validated, guided, online Cognitive Behavioral Therapy for Insomnia (CBT-I), provided via i-Sleep (which was made available on paper to participants) [122,123]. During the program, participants received information about the different stages of sleep, a healthy sleep pattern, how this pattern might change as we get older, and practical advice on how to improve sleep quality. The course consisted of the following modules: psycho-education, sleep hygiene, behavioral interventions (eg, stimulus control and sleep restriction), relaxation, and dealing with worrying or sleep-obstructing thoughts. Specific recommendations and restrictions were also provided to improve sleep quality and quantity, such as a proper diet, physical exercise, and refraining from smoking or using alcohol before bedtime.

### Low-Intensity Group

Participants randomized to the low-intensity intervention group received general lifestyle-related health information, addressing the aforementioned 5 lifestyle domains. Participants received this general information through information leaflets (1‐2A4), through email, once every 2 weeks. The information leaflets discussed the lifestyle domains but exclusively offered general health information without providing participants any individual or personal guidance based on their personal circumstances. For example, participants were generally told that a healthy diet promotes a healthy brain, and which kind of food components are promoted by the guidelines for a healthy diet, but participants were not guided or advised how their own personal diet should therefore be adjusted to fit these diet recommendations and guidelines.

The information of these leaflets was also handed to the high-intensity intervention group to ensure both groups were provided with the same general health advice.

### Outcomes

All outcome measures were measured at baseline (T0) and after participation in the 6-month multidomain lifestyle intervention (T1), during visits at both research centers. Blood drawing and breath tests were performed in a fasted state. Some outcome measures, such as lifestyle domain or adherence-related questionnaires, were also collected throughout the intervention period. For a detailed overview of all outcomes and the collection schedule, see S4 in Multimedia Appendix 1.

### Primary Outcomes

The primary outcomes are the changes between baseline (T0) and follow-up after 6 months (T1) in:

Brain activity during working memory in dlPFC [124] and hippocampus (Harvard-Oxford atlas), using fMRI blood-oxygen-level-dependent (BOLD) activity and task accuracy during a numerical N-back task [125];Cerebral perfusion levels, measured by MRI arterial spin labeling in dlPFC and hippocampus;Peripheral immunometabolic biomarker levels in blood plasma (inflammation markers IL-6, TNF-α, hs-CRP) and feces microbiota diversity (Shannon- and phylogenetic diversity) and richness (Chao1).

In addition, we will investigate intervention-induced gut-immune-brain links by assessing the relation between the effects found in the abovementioned primary peripheral markers and brain outcome measures.

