There are numerous studies showing that gut microbiome composition and immune-metabolic health effects on the host are modified by diet and nutritional components [90-92], including the Mediterranean-type diets [93,94]. In addition, other lifestyle components such as physical activity [95,96], stress [97], and sleep [98,99] are known to affect the microbiota composition and intestinal health, as well as immune, vascular, and metabolic health [100-107]. Importantly, we hypothesize that multiple lifestyle domains can synergistically affect peripheral markers and should therefore be targeted simultaneously. However, it is still largely unclear how gut microbiome, immune, and metabolic factors link to brain health in aging, and which mechanisms are involved. By investigating how lifestyle-induced changes in these peripheral factors relate to changes in brain health, we can make stronger conclusions about the role of these peripheral-brain links in cognitive aging. Moreover, elucidating peripheral-brain mechanisms might also explain individual differences seen in lifestyle interventions for healthy cognitive aging.

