### Study Objectives and Hypothesis

We designed the HELI study (derived from the Dutch “HErsenfuncties na LeefstijlInterventie,” meaning “Brain function after lifestyle intervention”) to better understand the neurocognitive effects of a multidomain lifestyle intervention and underlying peripheral (central) mechanisms. The HELI study is a 6-month multidomain lifestyle intervention in older adults at risk of cognitive decline (based on lifestyle-modifiable cardiovascular risk factors) with a high and low-intensity intervention arm. We focus on 5 different lifestyle domains within the intervention period: diet, physical activity, stress management and mindfulness, cognitive training, and sleep. We will assess effects on multiple neuroimaging brain measures (primary: working memory task-related fMRI responses and performance, and quantitative imaging of CBF), peripheral measures related to the gut-immune-brain axis (primary: blood inflammatory profile and fecal microbiota composition), as well as their connections. We propose that, compared to the low-intensity group, the high-intensity group will show greater improvement in central neuroimaging outcomes (eg, fMRI and CBF) as well as peripheral outcomes (eg, blood inflammatory profile and fecal microbiota composition). Moreover, we hypothesize that individual changes in central outcomes correlate with changes in peripheral outcomes, as summarized in Figure 1.

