### Methods: Statistics and Analysis

We will test for change between T0 and T1 in the primary and secondary outcome variables, both within-group and between-group, using linear mixed-effect models with random effects for intercept (individuals). The intervention group and time will be included as fixed effects, as well as the interaction term between intervention group and time, to model the difference in change between T0 and T1 as a function of group allocation.

In addition, we will test for correlations in change (T0 minus T1) between (primary) brain outcomes and (primary) peripheral outcomes. We will select an appropriate correlation test for our data, based on whether assumptions are met. We will include both the high- and low-intensity groups if there is enough variance in change across both groups; else, we will only include the high-intensity group.

The level of significance will be set at 0.05 (2-sided). FDR correction will be used to account for multiple comparisons of secondary and exploratory outcomes. FWE correction will be used for secondary whole-brain analyses.

As part of exploratory analyses to assess the domain-specific effects on our primary outcome measures, we will take the pre- and posteffects of the primary outcome measures and use domain-related questionnaire scores and smartwatch-derived physiological data as a measure of improvement for each respective domain as predictors in linear mixed-effect models.

We will perform an intention-to-treat analysis. Participants who withdrew from the study during the 6-month intervention period, but had not withdrawn consent, were invited to the T1 (after week 26) follow-up outcome assessments. This means that we will use all available collected data, including collected (follow-up) data of participants who dropped out of the intervention. Missing data or data with insufficient quality, however, will not be used in the analysis.

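### A correlation of individual changes, pooled or in the high-intensity arm alone, cannot by itself show that gut-immune-brain links are intervention-induced

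*Protocol article*

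**What the plan says.** The Abstract and the Primary Outcomes section of the protocol article both describe the links to be studied as intervention-induced. Primary Outcomes puts it as "we will investigate intervention-induced gut-immune-brain links by assessing the relation between the effects found in the abovementioned primary peripheral markers and brain outcome measures".

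Methods: Statistics and Analysis gives the method: "we will test for correlations in change (T0 minus T1) between (primary) brain outcomes and (primary) peripheral outcomes". The type of correlation is left open ("We will select an appropriate correlation test for our data, based on whether assumptions are met"). The analysis set follows a rule: "We will include both the high- and low-intensity groups if there is enough variance in change across both groups". Where that condition fails, the fallback is worded as "else, we will only include the high-intensity group".

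The same section uses randomised group in the mixed models for single outcomes, where a group-by-time term serves "to model the difference in change between T0 and T1 as a function of group allocation". It states no group term, arm comparison or mediation model for the correlation analysis.

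Study Objectives and Hypothesis is more modest: "we hypothesize that individual changes in central outcomes correlate with changes in peripheral outcomes". The Introduction (Gut-Brain Axis and Peripheral Mechanisms) expects more of the analysis: "By investigating how lifestyle-induced changes in these peripheral factors relate to changes in brain health, we can make stronger conclusions". Those conclusions are meant to concern what part such links play in cognitive aging.

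**The concern.** The label and the test answer different questions. The label concerns what the intervention caused. A correlation test asks whether two changes co-vary for any reason. Over six months, inflammation, microbiota, blood flow and BOLD response could move together through illness, weight drift or changed medication, whatever the coaching did.

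The randomised comparison could help to separate these explanations, but neither version of the planned analysis uses it. The pooled version merges the arms, and the fallback drops the low-intensity arm altogether.

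This is not a detail left to an analysis plan. The article names the change score, the kind of test and the inclusion rule. The one choice it leaves open, which correlation coefficient to use, brings in no comparator.

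At stake is the mechanistic conclusion, which is the trial's stated purpose. A significant correlation in the high-intensity arm could be reported as intervention-induced when the low-intensity arm would show the same one.

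**Working it through.** **The plan's own figure.** The Sample Size section gives no figure for the correlation analysis. Its 90 participants are for the group-by-time effect with f(V) = 0.30, 80% power and α = 0.05. With λ = N·f² = 90 × 0.09 = 8.1 on 1 and 88 degrees of freedom, power is 0.804, and 90 is the smallest N that reaches 0.80. The figure reproduces but says nothing about correlations.

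**Inputs.**
- Randomised: 53 high-intensity, 49 low-intensity (Results).
- Data loss: 15% (Sample Size). 53 × 0.85 = 45.05 and 49 × 0.85 = 41.65, so about 45 and 42 analysed.
- Two-sided 0.05 (Methods: Statistics and Analysis).
- Correlation of changes shared by both arms, ρ: not in the document. Assumed 0 to 0.3.

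**Step 1: how often the planned test is significant when both arms share ρ and the intervention shifts neither marker.** By Fisher's z, the probability is approximately Φ(δ − 1.96) + Φ(−δ − 1.96), with δ = atanh(ρ)·√(n − 3). Here √42 = 6.481 for the high-intensity arm alone (n = 45) and √84 = 9.165 for both arms (n = 87).

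| ρ | atanh(ρ) | δ high only / pooled | Approximation | Simulation (40,000 runs) |
|---|---|---|---|---|
| 0 | 0 | 0 / 0 | 5% / 5% | 5% / 5% |
| 0.1 | 0.1003 | 0.65 / 0.92 | 10% / 15% | 10% / 15% |
| 0.2 | 0.2027 | 1.31 / 1.86 | 26% / 46% | 26% / 46% |
| 0.3 | 0.3095 | 2.01 / 2.84 | 52% / 81% | 53% / 81–82% |

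With no data loss (53 and 49), the simulated rates are 31% / 52% at 0.2 and 60% / 87% at 0.3. The test has its correct size at ρ = 0, so the issue is what a rejection means.

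**Step 2: does adding arm as a covariate cure this?** No. At 45 and 42 with ρ = 0.3, the arm-adjusted rate is 81%. Arm adjustment does solve another problem. If both outcomes shift by 0.6 SD in one arm and are uncorrelated within arms, the unadjusted pooled test is significant in 12% of runs and the adjusted test in 5%.

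**Step 3: a between-arm difference in correlation.** Its standard error on the z scale is √(1/42 + 1/39) = 0.222. In the Step 1 scenarios it rejects in about 5% of runs at every ρ. Its power is modest. For 0.4 against 0, 0.4236/0.222 = 1.91, giving about 48% (49% simulated). For 0.5 against 0, 0.5493/0.222 = 2.47, giving about 70%. For 80% power, (1.960 + 0.842) × 0.222 = 0.62, which is a correlation of about 0.55 against 0.

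**Step 4: is that difference the right sole criterion?** No. Let coaching shift the peripheral marker by 0.6 or 0.8 SD, and let the brain outcome follow with the same slope (0.3 to 0.5) in both arms; these values are assumed. The brain effect is then wholly caused by the intervention. A mean shift changes neither arm's slope nor its correlation, so the Fisher z comparison and the arm-by-change interaction each reject in only about 5% of simulated runs.

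**The case against.** The strongest reply is that the article describes a pathway: lifestyle change moves peripheral markers, and these affect the brain. The Discussion speaks of finding mediators. Under that model the relation can be equal in both arms, so equal correlations do not prove the absence of an induced link. The group-by-time models already test whether the intervention shifts each primary outcome, and the reference to effects found can be read as building on those tests. All of this stands. It limits the Step 1 rates to the case in which neither marker is shifted, and it rules out a between-arm difference as the only criterion. It does not rescue the plan, because the article does not make the correlation conditional on the group-by-time results, and a pooled or single-arm correlation cannot tell this pathway from no intervention effect.

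Three stronger readings are tempting, but the document does not support them:
- A reader might infer that any co-variation will be declared intervention-induced. No such decision rule is written; the statistics section speaks only of correlations in change, and the hypothesis only of changes that correlate.
- A reader might take the Introduction as evidence of background co-variation. It describes the human findings as mainly cross-sectional, which concerns differences in level between people and not correlated six-month changes within them. It also calls the link still largely unclear.
- A reader might treat the low-intensity arm as a picture of no intervention. That arm receives leaflets on all five domains, so a correlation there may be partly lifestyle-induced too.

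**Conclusion.** The point holds as a mismatch between the causal label and the fixed analysis. A correlation of changes, pooled or in the high-intensity arm alone, cannot by itself carry the label, and the fallback removes the randomised comparator.

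If both arms share a correlation of 0.1 to 0.3 and neither marker is shifted, the planned test is significant in 10% to 53% of trials (high-intensity arm only) or 15% to about 81% (pooled). These figures assume bivariate normal changes, 45 and 42 analysed, and a shared correlation that the document does not give; at zero the rate is 5%. They should not be read as a general false-positive rate for the trial.

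**What to change.** In Methods: Statistics and Analysis, or in the analysis plan:

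1. Always include both arms and delete the high-intensity-only fallback.
2. Model brain change on peripheral change with arm included. Report the two arm-specific correlations side by side, with the arm-by-peripheral-change interaction as supporting information.
3. Describe a pooled or within-arm correlation as an association of changes (co-change).
4. In the Abstract, Primary Outcomes and later reports, reserve intervention-induced for links that the randomised contrast supports. One route is a group-by-time effect on both the peripheral marker and the brain outcome together with an arm-adjusted association, as a mediation-type analysis with its no-confounding assumption stated. The other is a between-arm difference in the relation. Do not require the second route alone.
5. State that any arm contrast measures the added effect of high-intensity coaching, since both arms receive lifestyle information.

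The cost is wording and a few model terms per pair of outcomes; no new data are needed. The downside is that fewer links will qualify, given about 49% power for a between-arm difference of 0.4 against 0 and 70% for 0.5 against 0. A minimal alternative is to keep a correlation analysis and drop the causal label.
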